### **Standard of Care**

The stepped-wedge design allows each site to serve as its own control. Based on our preliminary data, it appears that some but not all clinicians screen for smoking behaviors. Few clinicians provide brief interventions or referral to treatment. To ensure each site has a similar baseline at the beginning of the study, each site will receive a short-quit smoking brochure that each clinic can provide to patients who are identified as smokers. This approach is often used as a control condition for smoking cessation efficacy trials, and we believe it will be useful in our planned effectiveness trial as well.

### **Retention**

We have maintained high viral load suppression and retention rates under the ABLE project. We will leverage the current approach and include additional strategies such as information leaflets about the importance of retention, appointment cards, motivational text messages, and phone calls (and home visits) to remind participants of appointments. All participants who miss study visits will be contacted.

### **Criteria for Stopping**

Withdrawal will take place in the case of significant side effects or at a participant’s request.

Psychiatric emergencies: If suicidal ideation or intent is observed, the study suicide prevention plan (SPP) will be implemented, and the participant will be withdrawn. The SPP consists of immediate psychiatric evaluation, use of a suicide prevention contract, provision of 24-hour access to a physician, and referral to emergency services.

## Study Procedures

### **1. Adaptation of SBIRT**

We will draw on the input of stakeholders such as the Anti-tobacco Network, and our experience working in the HIV care system in Botswana to integrate the use of LHWs. Nesting of the trial within ABLE allows our team including the front-line HIV care team to gain sufficient experience with the interventions. We will lead the formal training which will take 1 week and will emphasize interactive activities such as roleplaying. To ensure sufficient assimilation of training materials, LHW case managers must pass a post-training examination. The 5“A”s already has established theory-informed and evidence-supported methods and strategies to achieve behavior change. New training materials and revisions to the existing LHW case manager standard operating procedures will be piloted. We will hold a pre-implementation workshop with implementation leaders, LHW case managers, and NPDs to discuss the proposed integration of smoking cessation interventions into their scope of work. Training slide sets and materials will be reviewed. Feedback will be solicited on how to successfully adapt LHW case managers for smoking cessation interventions, and stakeholders will be provided with the opportunity to contribute. Engagement of these staff and key informants will ensure strong buy-in and robust sensitization on the outpatient service when we are ready to implement.

### **2. Site Integration and training for SBIRT**

Based on our experience with SBIRT implementation, we identified the following areas for its integration into a clinical setting.

**Site Engagement:** The clinical director or administrator of each facility will be asked to sign a Memorandum of Understanding committing to the BSMART study implementation.

**Care Team Staffing:** Four implementation leaders at country level, and two LHW case managers and two nurse prescribers/dispensers, will be identified at each of the facilities, the majority of whom are already dedicated to PLWH-centered counseling and HIV treatment management. Implementation leaders will be trained to be trainers on motivational interviewing and the components of the BSMART intervention. Before each implementation period, the implementation leaders will facilitate a 3-day kick-off orientation for the BSMART study and train LHWs and NPDs from sites to be activated at a central location. They will also provide in-service training as needed. The study investigators will provide a wide array of resources e.g. training materials, implementation procedures, and host regular calls with the implementation leaders to support implementation efforts.

**Clinical Skill Set:** Training for all implementation leaders will be scheduled and led by [name]. The training will introduce the study and provide the background and orientation to the 5”A”s and its assessment form.

**Medical Management:** A similar training will be provided for implementation leaders who in turn will train all licensed clinicians eligible to prescribe varenicline. This training will be scheduled and led by [name]. The training will provide the background and orientation to treatment with varenicline. A consultation group will be established to address questions clinicians may have when prescribing varenicline.

**Workflow Processes:** We will review how to integrate SBIRT into the care team. For example, we will have a LHW case manager in place at the outpatient clinics whose scope will be adapted to meet with the new and existing patients before the end of the clinic visit to introduce the study and conduct the 5”A”s. Other adaptations will include: 1) developing and piloting the new clinical workflow between LHW case manager and nurse prescriber/dispenser; 2) training the care team in implementing the new workflow; and 3) using monthly activity logs to track implementation strategies such as actions, methods, events, or efforts to promote adoption and implementation of SBIRT components.

### 3. **Establishing an Implementation Governance Structure for BSMART**

Guided by the Consortium for Cancer Implementation Science’s Tools for Stakeholder and Community Engagement, we will establish an implementation governance structure that integrates the voices of stakeholders, practitioners, and researchers (Figure 3).

[figure not shown]

**Figure 3. BSMART Implementation Governance Structure**

We consider our Stakeholders key to our research; not just in the role of providing advice, but as integral partners in all of our efforts related to the development, implementation and dissemination of our BSMART program.

The membership of the Stakeholder Advisory Group reflects the diverse constituents who are invested in the successful implementation of the smoking cessation program within the context of HIV service delivery. Drs. [name] and [name] will co-lead the Stakeholder Advisory Group activities. Drs. [name] and [name] will co-lead the Practitioner Engagement Group. The stakeholders have worked hand-in-hand as colleagues with the BSMART research team to select the intervention, develop the implementation design, and craft the dissemination plan. **Pre-engagement activities** during the proposal development prepare practitioners and stakeholders as well as researchers for meaningful engagement throughout the study. The shared goal of an equitable partnership means the creation of a conceptual framework for implementation and the **analysis plan** are designed to be meaningful for implementers and patients. These on-going focus groups meetings with our Stakeholder Advisory and Practitioner Engagement Groups should allow us to develop the conceptual framework with maximal input. For example, based on pre-engagement questionnaires with practitioners across HIV care clinics, we have included measures of competencies in delivering SBIRT.

The Stakeholder Advisory Group and Practitioner Engagement Core will monitor target enrollment milestones; assist with developing lay descriptions of the study; and inform outreach efforts to encourage diverse patient participation. Patient and stakeholder engagement helps to assure that intervention effects of treatment have face validity with patients. Part of monitoring the conduct of the project is contributing to the data analysis process and reviewing and interpreting results. By bringing patient, stakeholder, and practitioner' perspectives into the dialogue, patient partners will help to enlighten researchers regarding potential alternative explanations or interpretations. This process will lead to appropriate and culturally sensitive translation and dissemination of results. The interpretation and translation processes help to document which results are easy or difficult to understand and guide how best to bring the results to patients and other decision makers.

#### **4. Qualitative Research**

Pre-implementation – Two focus group discussions (one for nurse prescribers and one for LHW case managers) will be conducted as part of a two-day work-shop in which the SBIRT intervention will be introduced to LHW case managers and nurse prescribers who will be implementing the BSMART intervention in Step 1 sites. The focus will be their initial thoughts on SBIRT and how SBIRT can be modified to make it more culturally appropriate and feasible.

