## Methods

### Study Design

We will utilize a stepped wedge cluster randomized trial to implement BSMART. BSMART will be sequentially rolled out to 15 participating HIV treatment and care facilities assigned in three steps (Table 1). Each step will provide data for a 12-month control/pre-implementation, a 12-month implementation, and a 12-month maintenance period. We will stratify Botswana's HIV treatment and care facilities into three levels of facilities. We will randomly assign each of the three levels of facilities to one of three study steps. Each step will comprise (i.e. have representation) from three levels of facilities, giving each level of facilities the same probability of beginning the intervention at any step). We choose this design to:

- 1) minimize the practical, logistical, and financial constraints associated with large-scale project implementation,
- 2) control for the effect of time, and
- 3) ensure that all HIV treatment and care practices will eventually offer the intervention and assess maintenance.

The study will screen approximately 6,900 HIV-infected patients and we expect to enroll 750 eligible participants, 375 of whom will participate in the pre-implementation phase and 375 of whom will participate in the implementation phase across three waves of implementation at five facilities each.

| Table 1: Time Periods for Stepped Wedge Implementation |                                                  |         |                |                |                |             |
|--------------------------------------------------------|--------------------------------------------------|---------|----------------|----------------|----------------|-------------|
| Steps                                                  | Total Number of Participants                     | Year 1  | Year 2         | Year 3         | Year 4         | Year 5      |
| 1                                                      | 5 facilities, n=250 PLWH (1DH, 2 PHs, 2 clinics) | Control | Implementation | Maintenance    |                |             |
| 2                                                      | 5 facilities, n=250 PLWH (1DH, 2 PHs, 2 clinics) |         | Control        | Implementation | Maintenance    |             |
| 3                                                      | 5 facilities, n=250 PLWH (1DH, 2 PHs, 2 clinics) |         |                | Control        | Implementation | Maintenance |

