## **Randomization methods**

We have chosen 15 (and 4 reserved) high-volume (>1000 HIV-positive patients currently active and on ART) health facilities (See Figure 4) in the ABLE project for inclusion based on numbers of patients, accessibility to the research team, and willingness to collaborate. After a baseline period of 1 year, the BSMART intervention will be implemented in a step of five new randomly selected sites (1 district hospital, 2 primary hospitals, 2 primary care clinics) until it is eventually implemented in all 3 steps (15 sites). A computer-generated list containing facilities stratified by type will determine the order in which the sites receive the intervention. The randomization list will be maintained by a statistician who is not involved in the study, and the site allocation will remain concealed from the research team and clinical teams throughout the study and will be revealed for a given step only 1 month before the implementation of the intervention to allow for training.

[figure not shown]

Figure 4: Selected and reserve facilities for BSMART project

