## Study timeline

BSMART is a 5-year study:

Year 1: Protocol approvals will be obtained. A stakeholder meeting will be initiated. Standard operating procedures and manuals will be developed. Training of implementation leaders, lay health worker (LHW) case managers, nurse prescriber-dispensers (NPD), research assistants, and other facility healthcare workers will be conducted. Focus group discussions and Semi-Structured Interviews will be held with study participants, LHW case managers and NPDs.

Year 2: Screening and enrollment will be 12 months. In the trial, each participant will be followed for 24 weeks. Trial quality and compliance will be heavily monitored within the context of intervention implementation, data collection, and data quality.

Year 3: Qualitative studies on trial adoption and implementation delivery will be conducted. Participants' follow-up will be concluded.

Year 4: Analysis of trial primary endpoints and subgroup analysis will be conducted.

Year 5: Preliminary cost evaluation of the intervention will be conducted to focus on integration of the interventions into the HIV care system. Analysis for maintenance at the patient level i.e. durability of the intervention and at the facility level i.e. continuation with the interventions after the withdrawal of the interventions will be conducted. A final stakeholder meeting to focus on dissemination will be held.

|                                                                      | Year 1 |    |    |    | Year 2 |    |    |    | Year 3 |    |    |    | Year 4 |    |    |    | Year 5 |    |    |    |
|----------------------------------------------------------------------|--------|----|----|----|--------|----|----|----|--------|----|----|----|--------|----|----|----|--------|----|----|----|
| Timeline for Major Activities                                        | Q1     | Q2 | Q3 | Q4 |
| Data Management system in place                                      | X      |    |    |    |        |    |    |    |        |    |    |    |        |    |    |    |        |    |    |    |
| Stakeholder Advisory Group & Practitioner Engagement Group Meetings  |        | X  | X  | X  | X      | X  | X  | X  | X      | X  | X  | X  | X      | X  | X  | X  | X      | X  | X  | X  |
| Protocols, surveys, approval                                         |        | X  |    |    |        |    |    |    |        |    |    |    |        |    |    |    |        |    |    |    |

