| Adaptation of intervention through qualitative FGs with CMs and NPDs |        | X  | X  |    |        |    |    |    |        |    |    |    |        |    |    |    |        |    |    |    |
| U01 network meeting with NIH/NCI                                     |        |    | X  |    |        |    | X  |    |        |    | X  |    |        |    | X  |    |        |    | X  |    |
| Training of LHW CMs and NPDs                                         |        |    | X  | X  | X      |    | X  | X  | X      |    | X  | X  | X      |    |    |    |        |    |    |    |
| Recruitment and enrollment                                           |        |    |    | X  | X      | X  |    | X  | X      | X  |    | X  | X      | X  |    |    |        |    |    |    |
| Follow-up to 24-weeks (post intervention)                            |        |    |    |    | X      | X  | X  | X  | X      | X  | X  | X  | X      | X  | X  | X  | X      | X  | X  | X  |
| Interviews on feasibility and acceptability                          |        | X  | X  | X  | X      | X  | X  | X  | X      | X  | X  | X  | X      | X  | X  | X  | X      | X  | X  | X  |
| Analysis of trial outcomes                                           |        |    |    |    |        |    |    | X  | X      |    |    | X  | X      | X  | X  |    | X      | X  | X  | X  |
| Analysis of qualitative implementation data                          |        |    |    |    |        |    |    |    |        |    |    |    |        | X  | X  | X  | X      | X  |    |    |
| Preliminary cost evaluation                                          |        |    |    |    |        |    |    | X  | X      |    |    | X  | X      |    |    | X  | X      | X  | X  |    |
| Analysis of durability and HIV data                                  |        |    |    |    |        |    |    |    |        |    |    |    |        |    |    |    | X      | X  | X  |    |

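### Step 1 staff appear to meet SBIRT before their own control participants enrol, putting a third of the controls at risk of counselling contamination that the 90-day sensitivity analysis cannot address

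*Protocol*

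**What the plan says.** **Workshop.** Protocol, Study Procedures, 4. Qualitative Research, describes a two-day workshop with two focus groups: "SBIRT intervention will be introduced to LHW case managers and nurse prescribers who will be implementing the BSMART intervention in Step 1 sites". Attendees give first reactions and say how SBIRT could be adapted. The only timing is the label that places it before implementation.

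**Calendar.** The Study timeline chart has a row "Adaptation of intervention through qualitative FGs with CMs and NPDs", marked in the second and third quarters of Year 1. The row "Training of LHW CMs and NPDs" begins in the third quarter of Year 1, and "Recruitment and enrollment" begins in the fourth. The Year 1 narrative adds that "Focus group discussions and Semi-Structured Interviews will be held with study participants, LHW case managers and NPDs".

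**Periods.** Study Design states: "Each step will provide data for a 12-month control/pre-implementation, a 12-month implementation, and a 12-month maintenance period". It thus treats control and pre-implementation as one period. Table 1 gives Step 1 Year 1 as control and Year 2 as implementation.

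**Concealment.** Randomization methods says that the allocation stays hidden from the research and clinical teams and "will be revealed for a given step only 1 month before the implementation of the intervention to allow for training".

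**Control delivery and safeguard.** In the control phase the lay health worker (LHW) case managers give out the brochure (Enrollment in BSMART study; Table 2). The one analysis aimed at contamination, under Statistical Analysis for Study Objective 1, drops controls from the 90 days before crossover.

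**The concern.** The control condition is a brochure, and each site serves as its own control. If the LHWs who screen Step 1 smokers and hand them the brochure already know the 5 As and have discussed how to adapt them, some of that counselling may enter control contacts. Abstinence among Step 1 controls would then rise, the contrast within those sites would shrink, and Step 1 controls would differ in kind from those of Steps 2 and 3. The bias runs towards no effect. The planned safeguard looks only at the end of the control period, whereas this exposure would be present from the first control participant.

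**Working it through.** **1. Date the workshop.** Count months from the start of Year 1.

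| Event | Source | Months |
|---|---|---|
| Adaptation focus groups | Study timeline chart, Year 1 quarters 2 and 3 | 3 to 9 |
| First LHW and nurse prescriber training | Study timeline chart, from Year 1 quarter 3 | from 6 |
| First recruitment | Study timeline chart, Year 1 quarter 4 | from 9 |
| Step 1 control | Table 1, Year 1 | 0 to 12 |
| Step 1 implementation | Table 1, Year 2 | from 12 |

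Matching the workshop to the first row is an inference. The row names neither Step 1 nor a workshop, but no other row fits the stated purpose of adaptation through focus groups with these two staff groups.

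**2. Lead time against the disclosure rule.** Implementation at month 12 minus a workshop in months 3 to 9 gives 12 − 9 = 3 to 12 − 3 = 9 months. The rule allows 1 month, so the workshop is 2 to 8 months too early. The chart and Table 1 do not fit together, since recruitment from month 9 cannot fill a control year that starts at month 0. If the 12 control months run from first recruitment, implementation starts at 9 + 12 = 21, and the lead grows to 21 − 9 = 12 to 21 − 3 = 18 months. The conflict holds on either reading.

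**3. Controls concerned.** 5 facilities × 25 = 125 of 375, or one third.

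**4. What the 90-day exclusion leaves.** On the chart nobody enrols before month 9, and the focus groups end by month 9. With crossover at month 12, the exclusion removes roughly the whole fourth quarter, and with it nearly all Step 1 controls. With crossover at month 21, it leaves Step 1 controls who all enrolled after the exposure. In neither case does an unexposed Step 1 group remain for comparison.

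**5. Size, as an illustration only.** First, the plan's own power. Power and Sample size gives 25 per cluster per period, 5% loss, ICC 0.02, and 10% versus 20%; two-sided alpha is taken as 0.05, since no value is printed.

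- Analysed per cluster-period: 25 × 0.95 = 23.75
- Design effect: 1 + (23.75 − 1) × 0.02 = 1.455
- Effective n per group: 15 × 23.75 / 1.455 = 244.8
- Power of the two-proportion test (pooled variance under the null): 87.5%, against the stated 87%

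Now let Step 1 control abstinence rise by an assumed d points. The overall control rate becomes 10 + d/3.

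| d (assumed) | Control rate | Difference | Power |
|---|---|---|---|
| 0 | 10.0% | 10.0 points | 87.5% |
| 1 | 10.3% | 9.7 | 84.9% |
| 2 | 10.7% | 9.3 | 82.0% |
| 3 | 11.0% | 9.0 | 78.8% |
| 5 | 11.7% | 8.3 | 71.6% |

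The protocol supplies no value for d, and zero is possible. The table uses the simple calculation that reproduces the plan's figure; it is not a model of the stepped-wedge analysis.

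**The case against.** **The date is inferred.** The workshop text is undated. The Year 1 narrative is weak support: it puts participant interviews in Year 1, although Semi-structured Interviews places them at week 24, and the Qualitative Data table puts staff focus groups at month 3 of the intervention phase. This stands and limits confidence.

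**A reader might infer that Step 1 staff are taught SBIRT and that their control phase is contaminated.** The protocol does not support that. Staff are introduced to SBIRT and asked for views. The formal course is a separate three-day one with an examination, and LHWs also receive two days on standard of care. The control schedule contains no counselling session and no varenicline, so any leak would be counselling alone. The protocol shows staff exposure, not altered control care.

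**A reader might also infer that the workshop is what breaks concealment.** Under Table 1 only Step 1 sites collect control data in Year 1, so their step is evident once control enrolment opens. The workshop at most brings disclosure forward, and moving it would not restore concealment.

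**The workshop may not be the only early exposure.** The chart starts LHW and nurse prescriber training in Year 1 quarter 3. Some of this may be standard-of-care training, but that course is for LHWs only. Adaptation of SBIRT also describes an undated pre-implementation workshop with both groups at which training materials are reviewed, possibly the same event. This widens the concern.

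These points remove neither the timing conflict nor the gap in the contamination analysis.

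**Conclusion.** The point holds as an internal conflict and a risk, with moderate confidence. Read with its chart, the protocol has Step 1 staff meeting SBIRT before any Step 1 control enrols and 3 to 9 months before a Year 2 start, against a one-month rule. That exposes 125 of 375 controls to possible counselling contamination, biased towards no effect, which no planned analysis would detect. The conclusion rests on two things: matching the undated workshop to the adaptation row, and LHWs of the same cadre delivering the control condition. The amount of leakage is unknown, and the power figures above show only what assumed amounts would do. Early disclosure is secondary.

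**What to change.** Reconcile Study Design with Table 1, Adaptation of SBIRT, Qualitative Research, Randomization methods, Statistical Analysis for Study Objective 1, and the Study timeline on when staff of each step first meet SBIRT. Then choose one of two routes:

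- hold the Step 1 workshop, and any SBIRT training of Step 1 staff, in the disclosure month, after Step 1 control enrolment has closed; or
- run the Year 1 adaptation with the country-level implementation leaders and staff of facilities outside the 15 randomised ones.

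Under either route, state that no SBIRT material or training reaches staff of a facility still enrolling controls. Say which part of the Year 1 training row is standard-of-care training. Reword the concealment statement so that it agrees with Table 1.

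The cost is protocol wording and one rescheduled or restaffed workshop. Under the first route feedback comes late, with about a month to use it, and controls still within their 24-week follow-up when the workshop is held are not fully protected. Under the second, feedback is less specific to the Step 1 sites.
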